## Experimental design

### Ethical aspects

This project was approved (number 5.329.534, in 04/04/2022) by the Ethics Committee for Research with Human Beings at the Federal University of Pernambuco, as required by the current legislation (Resolution No. 466 of December 12, 2012). All volunteers, over eighteen years of age, in the study will be asked to write out an online authorization regarding the Free and Informed Consent Term, as instructed in resolution No. 466/12 of the National Health Council. There will be no payment for the participation of each volunteer; however, at the end of the research, a reward will be available for the full completion of the experiments.

### Project

We intend to investigate whether people remember and transmit information more often when attributed to a prestigious source, in a pandemic scenario. We will use an online platform to carry out an experimental study, without the need for follow-up. The experiment will be conducted in two distinct stages, a recall stage as well as a stage for transmitting the information, both of which will be based on a fictitious text offered to the participants. This text will contain information about the use of a drug for COVID-19. There will be four versions of the text, one for each role model to be tested. Each version will consist of the same information, but only the role model attributed to the information being transmitted will change.

Since the experiment will be carried out online, there will be no need for blinding, on the part of the researchers, in carrying out the experiment and analyzing the results. More information is provided below about the selection of information along with a detailed procedure of the experiments. All data from the survey will included as supplementary material in the final articles.

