### Elaboration of the texts

The texts will contain a brief contextualization of the pandemic scenario; then, a particular opinion about the use of the drug Postex in the treatment of COVID-19 will be reported and attributed to one of the role models. By attributing the opinion to the role models, we will describe the characteristics that may confer prestige onto them. In this way, we will be able to determine whether the prestigious role model influences the retention and transmission of information. The stories have approximately the same number of words, ranging from 123 to 129 (S1 File).

All texts have the same structure; first, the pandemic context; next, a model with an opinion on the use of the medication. The number of central propositions referring to each of the models is also equal (Table 2).

**Table 2 pone.0281991.t002:** Central propositions used in the story texts for the experiments on recall and transmission of information about COVID-19.

Central Propositions	
Contextualization	Pandemic context
Proposition 1	Characterization of the role model
Proposition 2	Support for use of the drug
Proposition 3	Decrease in the number of deaths
Proposition 4	Decrease in the number of hospitalizations
Proposition 5	Assertion that use is safe
Proposition 6	Success rates exceed failure rates
Proposition 7	Postex should be used

All texts will be randomized so that they have the same chance of being assigned to participants.

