Finally, the volunteer will undergo a recall test, where they will be instructed to recount their respective reading text as accurately as possible. The instructions are as follows: “*Write down what you can remember about the text you read previously*. *Be as accurate as possible and don’t worry if you cannot remember all of the information*. *You have 10 minutes to complete this activity*.” At the end of the activity, a self-reporting stage of multiple-choice questions (S4 File) will follow with: [i] Who do you trust to seek information about COVID-19? (Participants can choose more than one option, and the alternatives will be health professionals, family members, friends, politicians, among other day-to-day personalities) [ii] What is your biggest source of information about COVID-19? (They can choose more than one option, and the alternatives range from online to physical media, such as newspapers and magazines) [iii] Have you been affected by COVID-19? (The options here will be yes or no, if yes, they will be asked to what extent they were affected) [iv] Has any member of your family been affected by COVID-19? (The options are the same as for the previous question) [v] Have you been vaccinated against COVID-19? The objective of this step is to perform data triangulation between the model that the person claims to follow and the factor that influenced the recall. Upon completion, the participant will see a message of acknowledgment and appreciation and will then be removed from the platform.

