**Fig 3 pone.0281991.g003:**
[figure not shown]
Representation of a linear chain transmission study [30].

The initial phase of this experiment will be similar to the first experiment, from clicking on the research link right up until the surprise recall test.

Following this, the experiments differ because, after this recall activity, the participant will receive a further instruction: “*Now*, *please transmit the information you obtained from the reading material to someone else by writing it here*. *You have 10 minutes to complete this activity*.” This transmission activity was conceived with the idea of testing whether what the person remembers at first is what they transmit when requested (Fig 4). At the end of this activity, a self-reporting step will take place followed by a message of acknowledgement and appreciation before being removed from the platform. The product of the information recall will undergo a spelling and grammar check, carried out by the researcher the information will then be directed to the next participant in the chain (corresponding to the 2nd generation). This entire process is repeated until the fourth and final participant in the chain is reached.

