### Data analysis

To analyze the recall and transmission of information provided by each model in the texts, we consider the central propositions recalled and transmitted by the participants in each of the conditions presented in the texts. Central propositions are the key points of information in a narrative. In our texts, there are seven propositions for each model presented in each of the stories.

Each proposition was identified by its central subject (Table 2), which enabled the identification of the central propositions that were most commonly remembered by the volunteers and the models to which they belonged.

To determine which information is most likely to be remembered and transmitted, we will consider each proposition as a binary result (whether the participant remembered it or not). We will then perform a multilevel logistic regression, considering the participant as a random effect and as a fixed effect: Hypotheses 1 and 2—type of model (digital influencer, physician, politician, and family member). To test the validity of the statistical models, they will be compared with a null model (which will only consider the effect of grouping by participants using the X^2^; test for model adjustments, through the ANOVA function, and the maximum likelihood estimate. The tests will be performed in an R environment [32] using the package lme4 [33].

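### Online delivery does not justify waiving researcher blinding, because coding of the free-text recall and editing of the chain texts remain open to judgement

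*Protocol article*

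**What the plan says.** The Project section waives blinding of the researchers: "Since the experiment will be carried out online, there will be no need for blinding, on the part of the researchers". The same sentence sets the scope as "in carrying out the experiment and analyzing the results". No other reason is given.

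Four other places in the article bear on this:

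- **Raw data.** Under Recall stage, the participant is told: "Write down what you can remember about the text you read previously". The transmission stage uses the same recall task and adds a second written task. Both produce free text.
- **Coding.** Under Data analysis, "we will consider each proposition as a binary result (whether the participant remembered it or not"), and "there are seven propositions for each model presented in each of the stories". The matching rule is brief: "Each proposition was identified by its central subject (Table 2"). No scorer is named and no automated method is described.
- **Editing.** Under Transmission stage, the recalled text receives a spelling and grammar check, "carried out by the researcher the information will then be directed to the next participant in the chain". The Abstract mentions correction of spelling errors only.
- **What separates the arms.** Under Project, the four versions differ only in the role model. In Table 2, Proposition 1 is "Characterization of the role model".

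**The concern.** Running the study on a platform removes personal contact between researcher and participant, and lets an algorithm choose the text. It does not remove judgement from what is done with the answers. Someone or something must decide whether a paraphrase counts as, for example, Table 2's statement that success rates exceed failure rates. The protocol also has a person correct the wording that becomes the next reader's material.

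The hypotheses are directional: recall and transmission are expected to be greater for the prestigious source. If borderline answers are credited more readily when the text is seen to come from the influencer arm, the difference goes straight into the odds ratio for type of model. If grammar corrections clarify meaning more in one arm, later generations start from a better text, and that advantage is carried down the chain. Both hypotheses are exposed through coding, and Hypothesis 1 is also exposed through editing.

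**Working it through.** **1. What online delivery covers.** The steps of the experiment, set against the reason given for the waiver:

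| Step | Done by | Protected by online delivery? |
|---|---|---|
| Assignment of text version | Platform algorithm (Recall stage) | Yes |
| Presentation and time limits | Platform (Recall stage) | Yes |
| Coding of free text into seven binary outcomes | Not named (Data analysis) | No |
| Spelling and grammar check of chain text | The researcher (Transmission stage) | No |

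The reason supports the first two rows. The waiver extends to all four.

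**2. Can the arm be seen?** The arms differ only in the role model, and the role model is itself a scored proposition. An unmasked text that still mentions its source shows its arm, even with the arm code removed.

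**3. How many texts are edited as stimulus?** In a chain of four, the texts of generations 1 to 3 are passed on, so there are 3 hand-offs per chain. With four text versions the number is 3 × 4 × chains per version. The article gives three values for chains per version:

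- 16 (Transmission stage): 192 edited texts
- 21 (Sample size): 252
- 8 (Abstract): 96

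Those three values need reconciling in their own right. The size of any editing bias cannot be derived from the article.

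**4. Illustration for coding.** The article gives no figure for scoring error, so everything here is assumed: no true effect, true recall p in every arm, and d extra percentage points credited in the prestige arm only. Then

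OR = [(p + d)/(1 − p − d)] / [p/(1 − p)]

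- p = 0.10, d = 0.02: (0.12/0.88)/(0.10/0.90) = 1.23
- p = 0.10, d = 0.05: (0.15/0.85)/(0.10/0.90) = 1.59
- p = 0.40, d = 0.02: (0.42/0.58)/(0.40/0.60) = 1.09
- p = 0.40, d = 0.05: (0.45/0.55)/(0.40/0.60) = 1.23

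A second form of the assumption credits a share e of the truly absent propositions, so that observed recall is p + e(1 − p). For e = 2% and 5% it gives:

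- p = 0.10: OR 1.20 and 1.53
- p = 0.30: OR 1.07 and 1.18
- p = 0.50: OR 1.04 and 1.11

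Both forms show the same pattern: the distortion is largest when recall is low.

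**5. The plan's sample size.** The stated 327 is reproduced by the Demidenko formula with variance correction for a logistic Wald test: odds ratio 1.81, base probability 0.1, one-sided α 0.05, power 0.95, R² 0 and a standard normal covariate. The result is 326.2, rounded up to 327. The blinding point leaves this figure unchanged.

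**The case against.** **Hand-scoring is inferred.** Data analysis names no scorer, and who codes by which manual is detail an article may leave to the full protocol. This stands, so it should not be said that the researchers are documented as the scorers. The waiver itself, however, is a stated rule with a stated reason and extends to analysis. The researcher's role in editing is explicit.

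**The edit is limited.** It can alter a stimulus only for generations 1 to 3, and it concerns spelling and grammar, not content. This also stands. Grammar correction can still change or clarify meaning, and the Abstract and Transmission stage disagree on whether it is allowed.

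**There are safeguards.** The propositions are fixed in advance and equal in number across arms, and the Project section promises release of all survey data, so outsiders could rescore if the raw texts are included. That reduces the concern about coding. It cannot undo an edited text that participants have already read.

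**The size is easily over-read.** Three inferences are tempting, and the article supports none of them:

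- *That bias is shown.* The shifts of 2 and 5 points are assumptions. At 10% recall of seven propositions, a text has 0.7 hits on average; 5 points add 0.35, half as much again in one arm only, which is a severe scenario.
- *That 10% is the expected recall.* The 0.1 under Sample size is a software input chosen in place of the default of 0.2, not a forecast.
- *That an odds ratio of 1.59 can be set against the planning value of 1.81.* The planning calculation used a normally distributed covariate, so 1.81 there is an odds ratio per standard deviation, not a contrast between two arms.

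**Masking is imperfect.** Replacing source nouns leaves cues such as followers, influence and admiration (Table 1), and misspelt or paraphrased sources will escape a word list. This stands as a limit on the remedy, but partial masking still protects many judgements on Propositions 2 to 7.

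**Conclusion.** The point holds as a risk of differential bias. The article waives researcher blinding in conduct and analysis for a reason that does not reach outcome coding or the editing of texts passed on from generations 1 to 3. It does not show that bias will occur or how large it would be.

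On the assumed shifts of 2 to 5 percentage points in the prestige arm alone, with no true effect, the spurious odds ratio would be 1.23 to 1.59 at 10% recall and 1.09 to 1.23 at 40% recall. These figures depend wholly on the assumed shifts and recall rates. They show only that modest uneven scoring could matter. The waiver should be changed before scoring begins, and before chain texts are edited, because an altered stimulus cannot be corrected afterwards. Sample size and regression model are unaffected.

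**What to change.** Delete the waiver in the Project section and state the following instead.

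**Scoring**

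- Texts are exported for scoring without arm code and in random order across arms.
- The source wording and the description of the role model are masked before Propositions 2 to 7 are scored. The mask must cover descriptive phrases as well as nouns.
- Proposition 1 is scored separately, after Propositions 2 to 7 are complete.

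**Chain texts**

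- Reconcile the Abstract with Transmission stage by limiting the edit to spelling, under a fixed written rule or an automated spell-check.
- The edit is made without the arm code shown.
- The original and edited versions are both kept and released with the data.
- The source word is not stripped and restored in the stimulus. It is the one element the experiment manipulates, and an error there would corrupt the comparison.

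The cost is a little data-handling work. Masking will be incomplete, because some texts will still reveal their arm, and the report should say so.

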### Sample size

Individuals aged 18 years and older with access to the Internet will be selected to participate in the research. The recruitment of volunteers will be carried out through the dissemination of the survey on social networks such as Instagram, Twitter, Facebook, WhatsApp, and E-mail. To determine the sample size for the recall stage, we used the G*Power 3.1.9.7 software [25]. We conducted an *a priori* analysis to determine both the sample size and its power. As a basis for the study, we took the effect size (Odds ratio = 1.81) in a study by Bonin et al. [26] as it is the most recent study that brings memory-related variables and employs the same statistical test that we propose to use. We calculated a sample size of 327 people with an explanatory power of 95% and z = 1.64. The default for Pr(y = 1|x = 1)H0 in the G*Power software is 0.2 (i.e., a 20% probability of the event occurring if the null hypothesis is true). However, we use 0.1 to obtain an even more reliable sample size for the phenomenon we are investigating. We consider an α of 0.05, a Power (1-β err prob) of 0.95, R^2^; = 0, and normal distribution. Fig 1 presents the parameters used for this calculation.

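### The 327 people and 95% power belong to a one-sided test of one continuous predictor with one outcome per person, so 95% is not established for the planned four-text mixed model

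*Protocol article*

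**What the plan says.** The Sample size section of the protocol article bases the recall stage on a G*Power calculation. The effect comes from an earlier memory study: "we took the effect size (Odds ratio = 1.81". The error rates are given as "We consider an α of 0.05, a Power (1-β err prob) of 0.95". On the base probability the authors depart from the software default of 0.2: "However, we use 0.1 to obtain an even more reliable sample size for the phenomenon we are investigating". R² is set to zero, and the predictor is described by the words "0, and normal distribution". The result is: "We calculated a sample size of 327 people with an explanatory power of 95% and z = 1.64". The section adds that the source study uses the same statistical test as this one proposes. The transmission stage takes over the same parameters.

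The design and analysis are described elsewhere. Under Elaboration of the texts: "All texts will be randomized so that they have the same chance of being assigned to participants". Under Data analysis, each of seven propositions is a binary outcome, the participant is a random effect, and the fixed effect is "type of model (digital influencer, physician, politician, and family member"). The model is compared with a null model by a chi-square "test for model adjustments, through the ANOVA function".

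**The concern.** The calculation and the analysis differ in four ways: type of predictor, number of parameters tested, direction of the test, and outcomes per person. An odds ratio of 1.81 per standard deviation of a continuous covariate carries much more information than the same odds ratio between one text and the others. A one-sided test of one coefficient is also easier to pass than a non-directional 3-df test. Against this, seven outcomes per person add information that the calculation ignores. The net effect depends on how much participants differ, and the calculation has no term for that.

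At stake is how the result is read. If no effect of source is found, a stated 95% power invites the reader to take the null as strong evidence against prestige bias. The Introduction and Hypotheses sections already report conflicting evidence on recall. The same parameters serve the transmission stage, so both hypotheses are affected.

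**Working it through.** **1. Reproducing 327.** Inputs from the Sample size section: α = 0.05, power 0.95, odds ratio 1.81, base probability 0.1, R² = 0, normal predictor. So β0 = ln(0.1/0.9) = −2.197 and β1 = ln 1.81 = 0.5933. For a Wald test in simple logistic regression with variance correction:

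n = (z(1−α)·√V0 + z(1−β)·√V1)² / β1²

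- V1 is the slope variance per person under the alternative. With X ~ N(0,1), the information elements are 0.09627, 0.04132 and 0.10685, so V1 = 0.09627 / (0.09627 × 0.10685 − 0.04132²) = 11.22.
- V0 is the variance under the null at the same overall event rate of 0.1125: V0 = 1/(0.1125 × 0.8875) = 10.02.
- One-sided: (1.645 × 3.165 + 1.645 × 3.350)² / 0.3520 = 326.2, i.e. **327**.
- Two-sided: (1.960 × 3.165 + 1.645 × 3.350)² / 0.3520 = 389.7, i.e. 390.

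Without the variance correction the results are 345 one-sided and 415 two-sided; the Hsieh formula gives 342 and 411. Only the one-sided corrected version matches, and it agrees with the stated z of 1.64. Fig 1 is not shown, but the inputs in the text suffice.

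**2. Calculation and plan side by side.**

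| | Sample size calculation | Planned analysis |
|---|---|---|
| Predictor | one continuous, N(0,1) | four randomised texts, 327/4 ≈ 82 people each |
| Test | one coefficient | chi-square against null model, 3 df |
| Direction | one-sided | non-directional |
| Outcomes per person | 1 | 7 |
| Variation between participants | none | random effect |

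**3. Power of the planned 3-df test at N = 327.** Assumed pattern: influencer text at odds ratio 1.81 against three equal texts. Let P_t(k) be the probability that a participant given text t recalls k of 7 propositions, with logit p = β0 + β1·(influencer) + σu and u ~ N(0,1) integrated out. Let q(k) be the same quantity under the best-fitting null mixed model. Then

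λ = 2 × (327/4) × Σ_t Σ_k P_t(k)·ln[P_t(k)/q(k)], and power = P(χ²₃(λ) > 7.815).

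Power of 95% needs λ = 17.17. Recall is the rate for a participant with u = 0 given a non-influencer text. The 10% is the document's base probability; the 40% and all values of σ are assumptions.

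| Participant SD σ | 10% recall: λ, power | 40% recall: λ, power |
|---|---|---|
| 0 | 17.2, 95% | 35.6, above 99% |
| 0.5 | 14.7, 91% | 24.3, 99% |
| 1.0 | 9.5, 74% | 12.4, 85% |
| 1.5 | 5.8, 50% | 6.8, 58% |

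SDs of 0.5, 1.0 and 1.5 correspond to latent intraclass correlations σ²/(σ² + π²/3) of 0.07, 0.23 and 0.41. If 10% is instead the average rate across participants, power is slightly lower: 86% at a correlation of 0.1 and 58% at 0.3. Simulation of the same model (82 per text, 400 runs) gave 87.5% and 59.8% there.

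**4. A one-sided influencer contrast instead.** Under the same pattern, a 1-df contrast of the influencer with the pooled other texts has the same λ, and one-sided power is Φ(√λ − 1.645). For σ = 0.5, 1.0 and 1.5:

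- 10% recall: √λ = 3.83, 3.09, 2.41; power 99%, 93%, 78%.
- 40% recall: √λ = 4.93, 3.53, 2.61; power above 99%, 97%, 83%.

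**The case against.** The strongest reply is that the 3-df test need not be the hypothesis test. The article introduces the chi-square comparison as a check on the validity of the models. The four-level factor also yields coefficients, and the predictions are directional, which suits a critical z of 1.64. How contrasts are tested may be left to an analysis plan that is not shown. This stands in part: step 4 shows that a one-sided pooled contrast does better throughout. But the article does not declare that contrast, and the number reported was not computed for it or for any other comparison of texts.

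A reader might infer that the design simply lacks 95% power. The documents do not support that, because they fix neither the participant variance nor the expected recall. The 0.1 is presented as a choice made for a more reliable sample size, not as a forecast of recall. At 40% recall and a small participant SD, the 3-df test exceeds 95%.

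A reader might also quote power for one outcome per person, such as 24% for the 3-df test at 10% recall, or about 1,460 people needed for a binary predictor held by a quarter of the sample. Those figures leave out six of the seven planned outcomes, so they do not describe this design. Nor does the article require three simultaneous significant comparisons, so power for that rule is not a measure of the plan either.

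**Conclusion.** The arithmetic of 327 is right for the test it describes; that test is not the planned one. The 95% is therefore not established for the planned analysis. At the document's odds ratio and base probability, the 3-df test attains it only with zero participant variance, where the gain from seven outcomes happens to offset the loss from the four-level factor and the non-directional test. With variation between participants it falls, to 50% at the largest SD examined. At 40% recall the claim can hold or fail depending on the SD.

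This rests on the influencer-against-three-equal-texts pattern, on equal allocation, and on assumed SDs and an assumed 40% recall that have no source in the documents. The mismatch itself needs none of these assumptions. No single replacement figure can be derived from the article; only a range can.

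**What to change.** Keep the sample. Replace the power statement with power simulated from the planned model: about 82 people per text, seven propositions, a participant random intercept and the four-level factor. State the assumed recall rate, participant SD, sidedness, and the test or contrast used, and report the range over recall and SD. Either remove the z of 1.64 and the normal-distribution setting, or declare a one-sided influencer contrast as the hypothesis test and power that.

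For the transmission stage, first reconcile the number of four-person chains per text: 8 in the Abstract, 21 in the Sample size section and 16 in the Transmission stage section, i.e. 32, 84 or 64 people per text. Then simulate with dependence within chains included; reusing the recall-stage result would misstate power again.

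For the recall stage the cost is a few hours of simulation and possibly a less favourable stated power, with no extra participants. The transmission stage also needs a decision on the chain count.
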